## Methods/Designs

### Study Design

This is a randomized, sham-controlled double-blind study. Participants will be randomly assigned by main investigator to three parallel groups using computer-generated random numbers with a 1:1:1 allocation ratio, either receive (1) MA-related cues retrieval in VR combined with active TMS (group A: MA VR scene + TBS) or (2) sham TMS (group B: MA VR scene + sham TBS), or (3) neutral cues retrieval in VR combined with active TMS (group C: neutral VR scene + TBS). Participants, outcome assessors, and data analysts will be blinded to the group assignment during treatment sessions. The doctors delivering TMS treatment will know the allocation sequence but will not be involved in the assessment. Once treatment is completed, participants will be asked to guess the specified intervention they have received to determine the actual effect of TBS. Then the clinical evaluator will debrief the participants about the study procedures. The two “VR retrieval–TBS” treatment sessions will be scheduled in 2 days within 1 week using an MA-related or neutral VR scene. Clinical, psychological questionnaires and EEG will be carried out at baseline (T0), each treatment session (T1/T2), the week of the last treatment (T3) and over 1 month after treatment (T4), as shown in Figures 1, 2. This protocol follows SPIRIT recommendations.

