### Outcome Measures

#### Primary Outcome Measure

We will evaluate the short-term effects of Retrieval-TBS treatment in the reduction of cue-induced drug craving and cue reactivity by comparing EEG in VR scene between baseline (T0) and post-test (T3).

***EEG*** will be recorded by a portable EEG system (Muse by Interaxon Inc.) during each VR session (3 min/scene × 1 MA-related VR scene and 1 neutral-related VR scene = 6 min) at T0 and T3, respectively. Each patient will wear an EEG headset before entering the VR scenes. Four channels (refer to EEG 10-20 system: FP1, FP2, TP9, TP10) and an original reference (FPz) will be retained to measure the brainwave spectrum including delta, theta, alpha, beta and gamma (with a sample rate of 256 Hz and 12 bit resolution), frequency bands between 45 and 60 Hz were omitted because muse hardware applied notch filters at 50 and 60 Hz to reduce environmental noise (67). According to a previous study, there was a significant difference between drug-cue and neutral-cue-induced EEG activities (68). In terms of drug-cue related memory, the frontal theta activity used as a feedback signal in adaptive regulation was highlighted for memory updating (69), which has been suggested as an indicator of the enhanced binding of incoming interconnected information in memory formation (70), while the beta activity which reflects a memory promoting state (70) indicated the level of memory integration in reconsolidation (71). Since the wearable devices available in VR have been applied to classify emotional states (72), we plan to use wearable EEG combined with VR scenes to observe the brain activity associated with memory in the current study. The average power in EEG frequency bands (i.e., δ = 1–4 Hz, θ = 4–8 Hz, α = 8–13 Hz, β = 13–30 Hz, γ = 30–50 Hz) are real-time computed in hardware and sent alongside an indicator of data quality from each sensor. The Muse manufacturer provided on-device computed FFTs (https://sites.google.com/a/interaxon.ca/muse-developer-site/museio) were used to estimate the spectral power density (μV2/Hz) for frontal electrodes in each frequency band in this study. EEG spontaneous measures at the frontal sites were calculated, as shown in Figure 2, by 1 min post-dark data minus 1 min pre-dark data in each frequency band in each VR scene. We used state-related EEG to calculate the EEG activities for drug-related craving state in VR, because cue-induced craving is related to a tonic, slowly changing craving state and Muse is a portable device that may not stably acquire EEG activities during walking in VR scene. Previous studies have used “state-related EEG” to compare different EEG activities in different state (56, 72, 73). Because of the non-normal distribution, power density value and ratios were log-normalized. For statistical tests, a two-tailed alpha of 0.05 was used unless explicitly stated otherwise.

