### Participant Timeline

All participants will be introduced to follow the schedule of baseline phase, treatment sessions and follow-up test. All patients passing the screening process will enter the treatment procedure. Participants will be grouped into A, B or C to receive MA-VR retrieval combined active TBS (MA VR-active TBS) or MA-VR retrieval combined sham TBS (MA VR-sham TBS) or neutral-VR retrieval combined active TBS (neutral VR-active TBS), respectively. The treatment includes two TMS intervention sessions within 1 week. Each session takes about 30 to 40 min including preparation time, VR retrieval of 3 min, relaxation of 10 min and continuous TBS of 5 min. The post-test will be conducted 1 to 4 days after the last session and the follow-up test will be taken over at least 1 month later. The timeline for participants in this trial is illustrated in Figure 2.

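### Blinding is stated only for the treatment sessions and the debrief follows them, so as written the T3 primary outcome and all T4 data come after both

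*Protocol article*

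**What the plan says.** The Study Design section opens with "This is a randomized, sham-controlled double-blind study". It then gives the scope of the blind: "Participants, outcome assessors, and data analysts will be blinded to the group assignment during treatment sessions". The doctors who deliver TMS know the allocation but take no part in assessment.

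The same section sets what happens next: "Once treatment is completed, participants will be asked to guess the specified intervention they have received", and "Then the clinical evaluator will debrief the participants about the study procedures". It gives the purpose of the guess as establishing what TBS actually did.

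The Participant Timeline section defines the period: "The treatment includes two TMS intervention sessions within 1 week". For T3 it states: "The post-test will be conducted 1 to 4 days after the last session". T4 comes no sooner than a month afterwards.

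Under Primary Outcome Measure, the contrast is EEG at T0 against T3. Under Secondary Outcome Measures, EEG is repeated at T4, and the craving VAS, cue-induced heart rate, SAS, SDS and POMS-SF are collected at T0, T3 and T4.

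**The concern.** A sham arm protects a comparison only while participants and those handling the outcome data remain unaware of allocation, and that has to last until the outcome is recorded and analysed. Here the one sentence that defines the blind ties it to the treatment sessions, and the next planned contact after those sessions is a guess followed by a debrief.

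At stake is the contrast between group A (MA scene with active TBS) and group B (MA scene with sham TBS), which isolates the effect of stimulation. Craving is a momentary 0 to 100 self-rating, and anxiety, depression and mood are also self-report scales. A participant who has just been told how the sham and the memory-retrieval procedure work may rate differently according to what they believe they received. A difference between A and B could then partly reflect belief rather than stimulation, and the analysis could not separate the two.

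**Working it through.** No formula applies. The check is to put the protocol's own events in order and see where the outcomes fall.

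| Order | Event | Source | Inside the stated blinded period? |
|---|---|---|---|
| 1 | Baseline, T0 | Study Design | Before treatment |
| 2 | Two VR retrieval and TBS sessions, T1 and T2, within 1 week | Study Design; Participant Timeline | Yes |
| 3 | Guess of intervention, once treatment is completed | Study Design | No |
| 4 | Debrief on study procedures, next step after the guess | Study Design | No |
| 5 | T3, 1 to 4 days after the last session | Participant Timeline | No |
| 6 | T4, at least 1 month later | Participant Timeline | No |

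**Step 1: does treatment include T3 or T4?** No. Participant Timeline describes treatment as the two TMS sessions and dates the post-test from the last of them. The Abstract instead describes the first post-treatment assessment as 1 week after the intervention. That is also after treatment, so the order does not change.

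**Step 2: where do the defined outcomes fall?** Six measures are named: EEG, craving VAS, heart rate, SAS, SDS and POMS-SF. Each is collected at two post-treatment visits, so there are 6 × 2 = 12 combinations of measure and visit. All 12 fall in rows 5 and 6. One is the primary outcome (EEG at T3). Four of the six measures are self-report (VAS, SAS, SDS, POMS-SF), which gives 4 × 2 = 8 of the 12.

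**Step 3: is anything measured inside the blinded period?** Yes. EEG is recorded at T1 and T2, and each retrieval scene ends with a craving VAS. These are not the contrasts that define the primary or secondary outcomes, so they do not protect those contrasts.

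**Step 4: does other text extend the blind or delay the debrief?** None does. The Abstract and Study Design call the trial double-blind without saying until when. Data Collection and Statistical Methods does not mention blinding of the analysis.

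**Step 5: what does the stated scope give assessors and analysts?** Very little. The defined post-treatment assessments and the analysis all take place after the sessions have ended.

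**The case against.** The strongest reply is that this is loose wording rather than an intended lifting of the blind. Analysts have no role in treatment sessions, so a literal time limit would make the promise to blind them empty. The trial is called double-blind without qualification, and nothing says the blind ends before T3. The debrief also has no date: the Study Design section describes it before it sets out the T0 to T4 schedule, and the two figures that show the timeline are not available here. This is a fair reason for caution about intent. It does not remove the problem, because the sequence as written puts the debrief right after treatment and no text overrides it.

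Three stronger readings are tempting, and the document supports none of them.

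- A reader might infer that participants are told their arm. The debrief is described as covering study procedures, and disclosure of allocation is not mentioned. Participants asked to guess presumably know already that alternatives exist. The supportable claim is exposure to bias, not certain unblinding. Nor is the clinical evaluator who debriefs identified as one of the outcome assessors.
- A reader might infer that double-blinding cannot hold for group A against group C because C sees a neutral scene. Participants can see which scene type they receive, but everyone sees neutral and MA scenes at baseline. A participant's own scene does not reveal which arm is experimental, and assessors and analysts can still be blinded.
- A reader might infer that the EEG result would be pushed in the hypothesised direction. Band power is computed on the device, and the primary outcome section names no primary band or direction, so this cannot be claimed. The exposure for EEG is smaller than for self-report, though not nil, because the protocol treats the EEG measure as reflecting a craving state.

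**Conclusion.** The point holds as a matter of stated sequence and scope. Followed as written, all 12 post-treatment combinations of measure and visit, including the primary one, come after the stated end of blinding and after the debrief, for all 45 planned participants. The 8 self-report combinations are the most exposed.

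This rests on two readings: that the debrief directly follows the guess at the end of treatment, and that treatment means the two TMS sessions. The first is the plain sense of the text but is not dated; the second is stated. The size of any bias cannot be derived from the document, and none is asserted. The matter should be settled before participants reach T3, because a debrief cannot be undone.

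**What to change.** In the Study Design section:

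1. State that participants, outcome assessors and data analysts remain blinded until each participant's T4 is complete and the data are locked.
2. Move the debrief to after T4, and show it there in the participant timeline.
3. Keep the guess right after the last session, give no feedback on it, and report it by arm as a check on blinding. Remove the statement that it determines what TBS actually did.
4. Note that participants can see which scene type they receive at treatment.

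The cost is a few sentences of protocol text and a later debrief date. The debrief can be attached to the existing T4 visit, so no visits or staff are added.

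If the sponsor always meant the blind to run through T4, items 1 and 2 simply put that on record. If not, the double-blind description does not cover the defined post-treatment outcomes and should be qualified.

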**Figure 1 F1:**
[figure not shown]
Flow chart of the study design. VR, Virtual Reality; N/MA scenes, neutral/methamphetamine scenes (displayed by VR); cTBS, continuous theta-burst stimulation; OFC, orbitofrontal cortex; neurophysiological reactivity including electroencephalogram (EEG) activities and electrocardiography (ECG) activities in outcome measures.

**Figure 2 F2:**
[figure not shown]
Participants' timeline. VR, Virtual Reality; cTBS, continuous theta-burst stimulation; N/MA-VR, neutral/methamphetamine scenes displayed by VR; VAS, visual analog scale; EEG, electroencephalography; ECG, electrocardiography.

### Study Setting

This clinical trial will be conducted in Shanxi Drug Rehabilitation Center (Taiyuan, Shanxi Province, China) involving the “VR retrieval–TBS” sessions and a series of assessments (as described in outcome measures).

### Participants

Participants with MUD in Shanxi Drug Rehabilitation Center will be voluntarily recruited to this treatment. After initial confirmation, eligible participants will then be required to sign an informed consent. The number and reasons of exclusion individuals, as well as those who reject or withdraw consent will also be recorded. *Inclusion criteria:* Selected participants will have to (1) be clinically diagnosed with Amphetamine-Type Substance Use Disorder according to Diagnostic and Statistical Manual of Mental Disorders (DSM-5) criteria, (2) abstinence periods at least 2 weeks without obvious withdrawal symptoms (e.g., drowsiness and dysphoria), (3) be aged 18 and 45 years old, and be right-handed, (4) be able to speak and read Chinese, (5) sign a consent form before intervention procedure.

*Non-inclusion criteria:* Participants meeting at least one of the following criteria will not be enrolled in this study: (1) meeting the diagnostic criteria of any other psychiatric disorder under DSM-5; (2) using other kinds of drugs (e.g., heroin, cocaine) in the past 30 days; (3) having contraindications to TMS treatment (head trauma, epilepsy or the history of epilepsy, metal implant, pregnancy and so on); (4) having a history of mental illness or a family history of mental illness; (5) be insensitive to VR scene (identified at the baseline); (6) having received psycho-therapy or TMS intervention in the last 6 months; (7) receiving medication treatment recently; (8) illiteracy; (9) having visual or hearing problems; (10) the individual threshold of TMS was higher than 50% of the maximum output of the TMS equipment; (11) scheduled to receive psycho-therapy or medication treatment for the next 2 months. *Exit criteria:* Participants will be allowed to withdraw from the clinical trial if they (1) voluntarily wish to stop the TBS sessions; (2) can hardly tolerate any aversive reactions (e.g., itching, numbing) or have a desire for other treatments; (3) do not complete the TBS sessions for other reasons; (4) suffer from worsening symptoms such as enhanced craving.

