#### VR Retrieval

Two types of VR scenes containing a series of neutral or drug-cues respectively will be presented in this study. As introduced in our previous study (43), the VR neutral scene for VR interaction practice at the first time that the participants using VR devices will be, a room with a desk, two spheres, two cubes, two cylinders, a laptop, and a visual analog scale (VAS) presented on the wall of the room. The spheres, cubes and cylinders are interactive, which means they can be picked up or stacked in the VR environment using the handle. This scene for practice will be presented once for 5 min. Another neutral scene will be presented in the baseline test and post-test. The neutral scene will be presented for 3 min followed by MA scenes after a 1-min interval of darkness in between. This neutral scene is a room with a sofa, a coffee table, and a standing lamp. There are about 50 triangle, square, or cylindrical blocks on the coffee table, about 10 cm in diameter. All the blocks are interactive. There are two MA scenes. Both scenes will be presented in the baseline test and the post-test, each 3 min, with a 1-min interval in between. The first MA scene is a room with a sofa, a coffee table, a standing lamp, a wardrobe, and a cabinet. There are many items on the coffee table, including a small bag of MA, a roll of foil, a piece of foil, lighters, plastic beverage bottles, paper money, straws, tools for diluting and filtering MA (a beverage bottle with straws and filters), a cellphone and a laptop. A video of playing a card game is played on the laptop screen. There is a TV hanging on the wall, which can play dance music or gambling game videos through the VR handle. The second MA scene is a room with a bed, a coffee table, and a chair. The items on the coffee table are similar to those in the first MA scene. There is a male or female avatar on the bed doing a series of actions of taking MA. All sofas or beds in the virtual scene have seats of similar heights at the corresponding positions in the real room. The MA-related VR scenes that we would like to use have been validated for their effect on MA memory retrieval based on the data in our lab and previous studies (58). In the baseline test and post-test, after the three scenes (neutral, MA1, MA2), the VAS is presented on the wall of a room in VR. Two groups (MA VR scene + TBS, MA VR scene + sham TBS) will view either the first or second MA scene prior to TBS treatments. Another group (neutral VR scene + TBS) will view a neutral VR scene before TBS treatments. Each scene for memory retrieval will last 3 min at each treatment session with 1 min pre-dark and 1 min post-dark, ended by an embedded VAS for self-reported craving rating. Real-time EEG for brain activity will be recorded while the presentation of VR scene (see *Outcome Measures*).

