
#### Secondary Outcome Measures

The secondary outcome will focus on the long-term effects of repetitive treatments on drug-cue-induced response. Evaluations introduced in primary outcome will also be collected in the follow-up test (T4). Furthermore, self-reported craving in VAS as a subjective indicator for cue-induced drug craving, physiological parameter (cue-induced heart rate) and possible co-variables corresponding to substance-taking history, emotional and mental state will be measured with the clinical diagnosis and psychological questionnaires at baseline (T0), post-test (T3) and follow-up test (T4) respectively.

***VAS*** embedded in VR scenes is a 100-point visual analog scale ranging from 0 (no craving) to 100 (high craving) for self-reported craving. Each patient will be directed to evaluate their current craving at a black screen on one wall of a virtual room. They will be guided to focus on their momentary feeling to make an assessment. The VAS points at baseline (T0) will be compared with the post-test after the last treatment (T3) to identify an expected reduction in self-evaluated craving. The median, range, average and standard deviation of VAS will be calculated for analysis.

***Electrocardiography (ECG)*** Given the association of MA with autonomic nervous system dysfunction (74) and the significant difference in heart rate between drug-cue and neutral-cue in the cue-induced craving paradigm (75), ECG (BIOPAC ECG module, with sampling rate of 1,000 Hz) will be recorded in this experiment as an indicator of physiological changes. In addition, changes in the heart rate interval can reflect abnormalities of autonomic nervous function (76). In addition, its activities are related to executive functions such as working memory, attention maintenance, and response inhibition involved in prefrontal cortex activities (77). In MA studies, it shows significantly reduced heart rate variability in MA populations (76), and the difference between drug-cue and neutral-cue is significantly associated with subjective cravings (78). Therefore, ECG will be recorded at the same time with EEG.

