#### Inferential Statistics to Determine the Efficiency of Intervention

The statistical significance (sig) and effect size (ES) will be evaluated for treatment-effects determination either by paired *t*-test and repeated measures ANOVA test [two factors, test time (baseline vs. post-test) and treatment (MA VR scene + TBS vs. MA VR scene + sham TBS vs. neutral VR scene + TBS)] in parametric estimations or Friedman's chi-square and Kendall's W coefficients in non-parametric statistics. These differences between baseline and post-tests will be compared firstly between the three parallel groups for self-reported craving and neurophysiological measures (e.g., EEG and ECG).

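### Candidates insensitive to VR are excluded on the T0 session that is also the efficacy baseline, so within-arm T0-to-T3 change can reflect regression to the mean; the between-arm contrasts are not affected

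*Protocol article*

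**What the plan says.** All references are to the protocol article.

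- **Participants**, non-inclusion criterion (5), bars anyone found to "be insensitive to VR scene (identified at the baseline". No measure and no cut-off is given.
- **Study Design** lists the assessments as "baseline (T0), each treatment session (T1/T2), the week of the last treatment (T3"), followed by T4, so baseline means T0.
- **VR Retrieval** says of the two MA scenes: "Both scenes will be presented in the baseline test and the post-test". The only earlier VR exposure described is a neutral practice scene.
- **Primary Outcome Measure** evaluates the short-term effect by "comparing EEG in VR scene between baseline (T0) and post-test (T3").
- **Secondary Outcome Measures** says of craving: "The VAS points at baseline (T0) will be compared with the post-test after the last treatment (T3) to identify an expected reduction".
- **Inferential Statistics to Determine the Efficiency of Intervention** names the tests for deciding on a treatment effect. The parametric branch has a paired *t*-test and a "repeated measures ANOVA test [two factors, test time (baseline vs. post-test) and treatment" (the three arms). The non-parametric branch has Friedman's chi-square and Kendall's W. The section then adds: "These differences between baseline and post-tests will be compared firstly between the three parallel groups".
- **Data Collection and Statistical Methods** has eligibility checked before randomisation.

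**The concern.** The T0 session does two jobs. It decides who is reactive enough to enter, and it supplies the before value against which T3 is judged. A single reading of craving or reactivity contains day-to-day noise. Removing low readings keeps some people who happened to read high that day and drops some who happened to read low. The retained group's T0 mean is therefore too high relative to its own usual level, and T3 drifts back with or without stimulation.

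That drift has the same direction as the VAS result the plan hopes for, which it describes as comparing T0 with T3 "to identify an expected reduction in self-evaluated craving". The paired *t*-test and Friedman's test are within-subject tests, and the plan lists both for determining treatment effects. A fall within the group receiving MA scenes plus active TBS could therefore be read as a benefit when part of it comes from the eligibility rule. In the non-parametric branch this matters more, because the only tests named there are within-subject ones.

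**Working it through.** **1. The plan's own figure.** The document gives no figure for this selection effect. The nearest is N = 45 in Sample Size, based on the within × between interaction with f = 0.2496 (taken as printed), 3 groups, 4 tests, α = 0.05 and power 0.95. Assuming a correlation of 0.5 between tests and sphericity (neither is stated):

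λ = f²·N·m/(1 − ρ) = 0.2496² × 45 × 4 / 0.5 = 22.4, with df = (3 − 1)(4 − 1) = 6 and (45 − 3)(4 − 1) = 126.

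Power is 0.955 and 45 is the smallest N that reaches 0.95, so the figure reproduces. The test that sized the trial is the between-arm one.

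**2. Expected fall with no treatment effect.** Assumptions: normal scores, equal variance at T0 and T3, correlation ρ between them, and the lowest fraction q at T0 excluded on the analysed measure itself. In SDs of the unselected T0 measure:

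expected fall = (1 − ρ) × φ(z_q)/(1 − q)

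The factor φ(z_q)/(1 − q) is 0.195, 0.350 and 0.497 for q = 10%, 20% and 30%.

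| Excluded | ρ = 0.7 | ρ = 0.5 | ρ = 0.3 |
|---|---|---|---|
| 10% | 0.06 | 0.10 | 0.14 |
| 20% | 0.10 | 0.17 | 0.25 |
| 30% | 0.15 | 0.25 | 0.35 |

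For example, at 20% and ρ = 0.5: 0.5 × 0.350 = 0.175 SD.

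**3. False-positive rates.** Simulation of 20,000 trials, 15 per arm, bivariate normal scores, selection before randomisation, no treatment effect, two-sided tests at 5%, ρ = 0.5:

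| Excluded | Paired *t*-test, one arm | of which falls (nominal 2.5%) | Time main effect, N = 45 | Time × treatment |
|---|---|---|---|---|
| 10% | 6.3% | 5.2% | 9.8% | 5.0% |
| 20% | 10.2% | 9.8% | 23.0% | 5.0% |
| 30% | 16.0% | 15.9% | 42.0% | 4.8% |

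Over ρ = 0.3 to 0.7 and the same exclusion fractions, the paired test runs from 6.0% to 21.0% and the time main effect from 8.1% to 56.3%. At ρ = 0.9 with 10% excluded the paired test is at 5.4%. The interaction stays between 4.8% and 5.3% in every scenario run. The reason is simple: the expected fall is the same in each arm, so it subtracts out.

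**4. Screen on a different measure from the outcome.** For a VAS screen and an EEG outcome, say:

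expected shift = [corr(screen, T0) − corr(screen, T3)] × φ(z_q)/(1 − q)

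With correlations of 0.30 and 0.15 and 20% excluded: 0.15 × 0.350 = 0.05 SD. If the two correlations are equal, the shift is zero.

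**5. Direction for EEG.** The Introduction describes MA scenes as lowering gamma power and power in the delta, theta and alpha bands, and drug cues as raising beta. If reactivity were judged on EEG, regression to the mean would appear as a fall in beta but as a rise in the bands that the cues depress.

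**The case against.** The strongest reply is that the plan's efficacy test is already between arms. The T0–T3 differences are to be compared across the three groups first, the ANOVA includes treatment as a factor, and the sample size rests on the interaction. On this view the outcome sections only define which change is measured, and nothing says that a within-arm drop alone would prove efficacy.

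Much of this stands. A reader might infer that the exclusion rule biases the trial's main randomised comparison. It does not: eligibility is settled before randomisation and the interaction keeps its nominal error rate. What the reply does not remove is that the paired *t*-test and Friedman's test are listed for determining treatment effects, and that the VAS sentence describes a before-after reduction with no comparator.

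Three further limits also stand.

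- A reader might infer a spurious fall in the primary EEG outcome. The documents do not support that, because neither the screening measure nor the decisive band is given.
- A reader might picture a large artefact. No exclusion fraction is stated, the scenes are described as validated for MA memory retrieval, and at 10% excluded the effect is small.
- A reader might conclude that a separate screening session is required. An additional MA-scene viewing before T0 would be another cue-induced retrieval, also in the neutral-retrieval arm, in a trial where retrieval is part of the intervention. Enrolling reactive participants is a defensible choice in itself.

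**Conclusion.** The point holds for within-arm readings only. If VR insensitivity is judged on the VAS or a measure closely tied to the T0 outcome, a fall of about 0.06 to 0.35 SD is expected in every arm without any treatment effect, for 10% to 30% excluded and a T0–T3 correlation of 0.7 to 0.3. All of these are assumptions, including normality and direct selection on the analysed score, because the document states neither the measure nor the cut-off. It also rests on T0 being the first MA-scene viewing, which is how the article describes it.

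The paired *t*-test, Friedman's test, the time main effect and the VAS reduction are exposed. The EEG bias may be small, absent or reversed. The time × treatment comparison is unbiased and N = 45 is not affected. This should be corrected because the text offers an unprotected route to a claim of benefit, but it is not a threat to the randomised result.

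**What to change.** Change wording in three sections.

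- **Primary Outcome Measure** and **Secondary Outcome Measures**: state that T0-to-T3 change within an arm is descriptive. Express the EEG and VAS effects as differences between arms in that change.
- **Inferential Statistics**: state that the paired *t*-test, Friedman's test and the time main effect are descriptive only. Rest every claim of reduced craving or cue reactivity on group A (MA scene + TBS) versus B (MA scene + sham) and A versus C (neutral scene + TBS), by time × treatment or by T3 adjusted for T0.
- **Non-parametric branch**: name a between-group test of the change scores, such as Kruskal–Wallis across arms with rank-sum tests for A versus B and A versus C.

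The cost is text only. Sample size, visits and the eligibility rule stay as they are, and no extra VR session is added. What is given up is the option of claiming benefit from a before-after fall in one arm.
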